## Abstract

**Background:**

Parkinson’s disease is one of the most frequent causes of disability among the older adults. It is a chronic-progressive neuro-degenerative disease, characterized by several motor disorders. Balance disorders are a symptom that involves the body axis and do not respond to dopaminergic therapy used in Parkinson’s disease. Therefore, physiotherapy becomes an important intervention for the management of motor disorders. Originally, these rehabilitative approaches were based on empirical experiences, but several scientific evidences suggests that neuronal plasticity is exercise-dependent. In this context, robotic rehabilitation plays an important role because it allows to perform task-oriented exercises and to increase the number of repetitions and their intensity. This protocol study aims to evaluate the effectiveness of robotic-based intervention of the older adults with Parkinson’s disease, designed to improve the gait and to reduce the risk of falling.

**Methods:**

This study is a single-blinded randomized controlled trial. The primary outcomes are: risk of falling, gait performance and fear of falling measured through Performance-Oriented Mobility Assessment (POMA), instrumental gait analysis and Short Falls Efficacy Scale – International (FES-I), respectively. One hundred ninety-five patients with PD will be recruited and randomly divided into three groups, to receive a traditional rehabilitation program or a robotic rehabilitation using Tymo system or Walker View in addition to the traditional therapy. Assessments will be performed at baseline, at the end of treatment and 6 months, 1 year and 2 years from the end of the treatment. A 10-treatment session will be conducted, divided into 2 training sessions per week, for 5 weeks. The control group will perform traditional therapy sessions lasting 50 min. The technological intervention group will carry out 30 min of traditional therapy and 20 min of treatment with a robotic system.

**Discussion:**

The final goals of the present study are to propose a new approach in the PD rehabilitation, focused on the use of robotic device, and to check the results not only at the end of the treatment but also in the long term.

**Trial registration:**

NCT04087031, registration date September 12, 2019.

## Background

Parkinson’s disease (PD) is one of the most frequent causes of disability among the older adults. It is a chronic-progressive neuro-degenerative disease, characterized by motor disorders, such as bradykinesia (poverty and slowness in movement), resting tremor, stiffness, flexed posture and “small steps” gait, not least the balance deficit with consequent high risk of falling [1, 2].

Balance is a fundamental requirement that requires a complex network of sensory information integrations, in order to generate an appropriate motor response aimed at controlling body movement. The balance disorder occurs later during the PD and is a symptom that involves the body axis. It can be highlighted when the person walks or changes direction during the journey. Balance disorders do not respond to dopaminergic therapy used in PD. Therefore, physiotherapy becomes an important intervention for the management of motor disorders. The effects of bradykinesia, rigidity, altered proprioception, postural instability, freezing of the gait, in PD patients, are studied and known in rehabilitation [3–5]. The reduction of balance is considered a risk factor for falls [6–8]. Postural instability and consequent falls are among the main factors that determine the quality of life, morbidity and mortality of a person suffering from PD [3, 5, 7]. The guidelines for physical therapy in the PD recommend that patients undergo a course in preventing falls from the onset of the disease [5]. These pathological conditions are routinely treated through rehabilitative approaches aimed at improving the static and dynamic balance, the recovery of walking and the falls prevention [2, 3, 5–7, 9]. Originally, these rehabilitative approaches were based on empirical experiences, but several scientific evidences suggests that neuronal plasticity is “exercise-dependent” and constitutes the main mechanism that supports the effectiveness of physiotherapy treatment [9–13]. Recent reviews show that rehabilitation induces important clinical benefits particularly in walking speed and balance [9, 10, 12, 13].

In fact, exercise increases synaptic strength and influences neurotransmission, thus potentiating functional circuitry in PD patients, through mechanisms that include increased synaptic strength resulting from raised dopamine and glutamate neurotransmission within the basal ganglia accompanied by increased dendritic spine [14, 15]. Exercise training was also found to produce functional changes (assessed by means of functional Magnetic Resonance Imaging) in known motor learning related brain structures, with aerobic exercise training-dependent neuroplasticity in the central nervous system due to neurochemical changes in the striatum [16]. Synaptic plasticity, neurogenesis and increased cortical vascularization, are three proposed indirect mechanisms underlying physical training-related improvements in PD patients [17, 18]. Moreover, an increased corticomotor excitability [19] and an optimization of the medication intake by easing its absorption [17] may represent direct effects of the improvements seen after exercise training.

In this context, robotic rehabilitation performs an important role [10–12, 20–22]. Different studies [9–11] show that robotic balance training produces performance improvements that are also correlated with evident neurobiological changes in the cerebral cortex [9, 10].

In a recent systematic review and meta-analysis robot-assisted gait training (RAGT) showed better outcomes than conventional interventions on some motor aspects in PD [23], and greater advantages than treadmill training for individuals with freezing of gait-related disability were observed in another study [24]. Upper limb motor performances in patients with PD were also improved after motor training aided by high technological devices [25].

Moreover, there is increasing evidence that suggest the use of the latest computerized technologies could revolutionize conventional treatments and provide better rehabilitation in patients with neurological diseases such as PD, by providing safe and objective real-time assessments of behavior [26].

Thus, thanks to the opportunity offered by technology of providing and controlling the provision of repetitive training/tasks/exercises, that represents the key factor for successful rehabilitation strategies, we hypothesize that an improvement of the primary end point (balance and gait) may be obtained through the use of the systems.

### Study aims and objective

This protocol study aims to evaluate an innovative rehabilitation treatment based on robotics, for the older patients with Parkinson’s disease, designed to improve the gait and to reduce the risk of falling. The treatment involves the use of two robotic devices: Tymo system (Tyromotion, Austria), a wirelesss static and dynamic platform, for evaluating and rehabilitating posture, and Walker View (TecnoBody, Italy), a treadmill equipped with a sensorised belt with eight load cells and a 3D camera.

The primary aim is the evaluation of the effect of the rehabilitation treatment on the balance and gait of the older PD patient, as a result of the use of the Tymo system or Walker View, at the end of the treatment and at a 6 months, 1 and 2 years’ follow-up using POMA scale.

The secondary aims are:
the evaluation of the effect of the rehabilitation treatment on the gait speed of the older PD patients, as a result of the use of the Tymo system or Walker View, at the end of the treatment and at a 6 months, 1 and 2 years’ follow-up using instrumental gait analysis;the evaluation of the effect of the rehabilitation treatment on the fear of falling of the older PD patients, as a result of the use of the Tymo system or Walker View, at the end of the treatment and at a 6 months, 1 and 2 years’ follow-up using FES-I short form scale.

In addition, the study design will include use a standardized questionnaires and instrumental gait analysis, in order to collect data on the improvements with a mix-method approach.

## Methods/design

### Trial design

This study is a single blinded (outcome assessors) randomized controlled trial. One hundred ninety-five patients with PD will be recruited and randomly divided into three groups, to receive a traditional rehabilitation program or, in addition to the traditional therapy, a robotic rehabilitation using Tymo system or Walker View. Assessments will be performed at baseline, at the end of treatment and 6 months, 1 year and 2 years from the end of the treatment. For the duration of the study, patients cannot receive treatments through robotic devices but will continue to be followed as outpatients by our rehabilitation department.

### Study setting

The study is conducted at the Clinical Unit of Physical Rehabilitation, IRCCS INRCA, in the Ancona and Fermo branches, Italy. Assessments and treatments are conducted in the robotics laboratories.

### Trial status

At the time of the submission of this study protocol, data collection is ongoing.

### Participants

The inclusion criteria are:
Aged 65 and over;Capacity to consent;Hoen and Yahr scale: 1–3 stage;Functional Ambulation Category (FAC) ≥ 2;Ranking scale score ≤ 3;Stability of drug treatment for at least 1 month;Geriatric Depression Scale 5-items: negative;

The exclusion criteria are:
Failure to meet the inclusion criteria;Concomitant participation in other studies;Lack of written informed consent;Clinical dementia rating (CDR) score ≥ 3;History of syncopal episodes, epilepsy and vertigo not controlled pharmacologically;Serious dysfunction of the autonomic system;Severe behavioral syndromes not compensated by drugs;Concurrent neurological diseases;Severe systemic diseases with life expectancy < 1 year;Patients unable to follow up.

### Sample size

The Performance-Oriented Mobility Assessment (POMA) [27], a test widely used to assess walking ability and associated with equilibrium, is used to calculate the sample size [28]. Assuming a small effect size of 10% [29], it is estimated that the overall sample size needed to capture this effect size is of 153 subjects, assuming a statistical power of 80%, a significance level of 0.05, three groups and 5 repeated assessments (a baseline and 4 follow-ups) in an ANOVA model within-between interactions. Even assuming a 25% drop out rate, the total number required would be 195 subjects (65 for each arm).

It is hypothesized that this sample dimension is more than sufficient to grasp a variation also for secondary outcomes for which a treatment effect size is assumed of a similar or higher entity than that identified for the primary outcome [30, 31].

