### Recruitment

Patients are selected by the outpatient department at the Clinical Unit of Physical Rehabilitation, IRCCS INRCA, in the Ancona and Fermo branches. These patients are contacted to schedule a visit with the physician. Once the compliance with the inclusion and exclusion criteria of the study has been verified and the informed consent (see Supplementary file) has been obtained in triplicate, the doctor proceeds with the baseline evaluation and with acquisition of gait assessment parameters through Gait Analysis at the Movement Analysis Laboratory of the Clinical Unit of Physical Rehabilitation of the Ancona branch.

A randomization technique based on a single sequence of random assignments is used. A list of random numbers generated by the computer is used and subject is assigned a number based on their order of inclusion in the study. According to this technique, the 195 subjects are randomly assigned to one of the 3 study groups.

At the end of the treatment and after 6 months, 1 year and 2 years, the patients will be contacted again to schedule subsequent follow-up visits and upgrades. During the follow-up period, patients will be monitored through telephone interviews once a month, in order to monitor their health state.

Recruitment will run from August 2019 to August 2021.

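### 195 randomised patients do not leave the required 153 at the assumed 25% drop-out: they leave 146, and the matching total is 204

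*Protocol article*

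**What the plan says.** The Sample size section of the protocol article bases the calculation on the POMA score, with an effect size given as 10% and described as small. The test is the group-by-time interaction: "three groups and 5 repeated assessments (a baseline and 4 follow-ups) in an ANOVA model within-between interactions". At 80% power and a 0.05 significance level, "it is estimated that the overall sample size needed to capture this effect size is of 153 subjects".

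The next sentence allows for losses: "Even assuming a 25% drop out rate, the total number required would be 195 subjects (65 for each arm").

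The Recruitment section uses that total as the number to randomise ("the 195 subjects are randomly assigned to one of the 3 study groups"), and the Abstract and Trial design sections repeat it. The article gives no other drop-out rate, evaluable number or inflation rule. The Data analysis section names repeated measures ANOVA for comparing changes over time between groups.

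**The concern.** A drop-out allowance should leave the required number of patients after the assumed losses. That means dividing the required number by the retained fraction. The protocol's total is smaller than this division gives, so its three figures (153 needed, 25% lost, 195 recruited) cannot all hold.

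At stake is whether the trial has its stated power under its own planning assumption. The wording "Even assuming a 25% drop out rate" presents 195 as safe at that rate. The same section then relies on this sample size as more than adequate for the secondary outcomes. The last assessment is two years after treatment in patients aged 65 and over, so drop-out of this order is a planning case to be taken seriously.

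**Working it through.** **Inputs stated in the Sample size section:** 153 patients needed; power 80%; significance level 0.05; k = 3 groups; m = 5 assessments; drop-out d = 25%; total 195, or 65 per arm.

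**Inputs assumed here:** the 10% is read as Cohen's f = 0.10; correlation between assessments ρ = 0.5; sphericity ε = 1. The article gives neither ρ nor ε. They are needed only for the power figures in steps 1 and 3, not for step 2.

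**Step 1. Reproduce the 153.** For the within-between interaction with ε = 1, the noncentrality is λ = f²·N·m/(1 − ρ), with degrees of freedom (k − 1)(m − 1) and (N − k)(m − 1).

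- At N = 153: λ = 0.01 × 153 × 5/0.5 = 15.3, df = 8 and 600, power = 80.3%.
- At N = 150: λ = 15.0, df = 8 and 588, power = 79.3%.

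On these inputs 153 is the smallest total that reaches 80%, so the plan's base figure reproduces exactly. With f = 0.10 and ε = 1, other correlations do not give it: the requirement is 213 at ρ = 0.3, 183 at ρ = 0.4 and 123 at ρ = 0.6. With ρ = 0.5, ε = 0.9 would require 164.

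**Step 2. Check the drop-out allowance.**

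| Quantity | Calculation | Result |
|---|---|---|
| Total needed at 25% drop-out | 153/(1 − 0.25) | 204 (68 per arm) |
| Shortfall in recruits | 204 − 195 | 9 (3 per arm) |
| Patients left from 195 | 195 × 0.75 | 146.25, so 146 |
| Patients left per arm | 65 × 0.75 | 48.75, against 51 needed |
| Shortfall in evaluable patients | 153 − 146 | 7 |
| Largest drop-out 195 can absorb | 1 − 153/195 = 42/195 | 21.5% |

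Rounding to equal arms does not explain the gap, since 153 and 204 both divide by three. The common mistake of multiplying instead of dividing gives 153 × 1.25 = 191.25, so 192, which is not 195 either. It is true that 195 = 156 × 1.25, but 156 appears nowhere in the article, so how 195 arose is a guess. The finding does not depend on it.

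**Step 3. Effect on power.** At N = 146: λ = 0.01 × 146 × 5/0.5 = 14.6, df = 8 and 572, power about 78% (0.7795). With 49 per arm (N = 147) it is 78.3%. The loss against 80.3% is a little over 2 percentage points.

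**The case against.** The strongest objection is that the error is small and its consequence conditional. Power falls by about 2 points, and only if drop-out reaches 25%; up to 21.5%, 195 is enough. No endpoint, comparison or analysis changes. This stands, and it limits the weight of the point.

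Second, the power loss assumes that patients who drop out contribute nothing. The article names repeated measures ANOVA but says nothing about incomplete records. In its classical form that analysis drops patients with a missing assessment, so complete-case use is a fair inference, but it is an inference. A fuller analysis plan may specify something else. Many drop-outs would have been seen at the end of treatment, and a method using their partial data would lose less. This also stands as a qualification of the 78%. It does not make 195 the right inflation of 153: by adding patients for drop-out, the plan itself counts drop-outs as lost.

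Third, ρ, ε and the reading of 10% as f are not in the article, and Table 1 uses the same 10% as an expected improvement in POMA. The power at 146 does depend on them: with f = 0.10 and ε = 1 it would be 60% at ρ = 0.3 and 88% at ρ = 0.6. But those correlations do not yield 153. The power figures should therefore be quoted with their assumptions. The contradiction between 153, 25% and 195 needs none of them.

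**Conclusion.** The concern holds. The statement that 195 patients meet the requirement at 25% drop-out is wrong: 146 remain where 153 are needed, and the consistent total is 204. This is arithmetic on three figures in adjacent sentences and rests on no outside assumption.

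The consequence is modest: power of about 78% instead of 80% at the protocol's own drop-out rate, assuming f = 0.10, ρ = 0.5, ε = 1 and an analysis of complete cases only. The figure still needs correcting, because it is the trial's stated justification for its size and the target used throughout the article.

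**What to change.** Keep 195 and restate what it delivers. Suggested wording: *195 randomised patients (65 per arm) give 153 completers if drop-out is at most 21.5%. At 25% drop-out, 146 complete and power is about 78% (f = 0.10, correlation 0.5 between assessments, sphericity, complete cases); 204 patients (68 per arm) would be required to retain 153.* The authors should confirm or replace the correlation and sphericity values with those they used.

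The cost is one corrected sentence and a slightly less favourable stated power or tolerated drop-out. No extra patients are needed, and the target of 195 in the Abstract, Trial design and Recruitment sections can stay, which suits a trial whose data collection is already under way. If the sponsor prefers to keep the 80% claim at 25% drop-out, the target has to rise to 204, which is 9 more patients, and those sections must change with it.

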### Recruitment

Patients are selected by the outpatient department at the Clinical Unit of Physical Rehabilitation, IRCCS INRCA, in the Ancona and Fermo branches. These patients are contacted to schedule a visit with the physician. Once the compliance with the inclusion and exclusion criteria of the study has been verified and the informed consent (see Supplementary file) has been obtained in triplicate, the doctor proceeds with the baseline evaluation and with acquisition of gait assessment parameters through Gait Analysis at the Movement Analysis Laboratory of the Clinical Unit of Physical Rehabilitation of the Ancona branch.

A randomization technique based on a single sequence of random assignments is used. A list of random numbers generated by the computer is used and subject is assigned a number based on their order of inclusion in the study. According to this technique, the 195 subjects are randomly assigned to one of the 3 study groups.

At the end of the treatment and after 6 months, 1 year and 2 years, the patients will be contacted again to schedule subsequent follow-up visits and upgrades. During the follow-up period, patients will be monitored through telephone interviews once a month, in order to monitor their health state.

Recruitment will run from August 2019 to August 2021.

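### One allocation sequence in order of inclusion does not ensure 65 per arm and leaves balance by branch to chance, at a small cost in precision

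*Protocol article*

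**What the plan says.** The Recruitment section of the protocol article describes the allocation method directly: "A randomization technique based on a single sequence of random assignments is used". It adds that a computer-generated list of random numbers is used and that each "subject is assigned a number based on their order of inclusion in the study". By this method "the 195 subjects are randomly assigned to one of the 3 study groups". Blocks, strata and fixed arm totals are not mentioned.

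The Sample size section states that "the total number required would be 195 subjects (65 for each arm", which implies 1:1:1 allocation. The Study setting section places the trial "in the Ancona and Fermo branches, Italy". The number of patients expected from each branch is not given.

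The Data analysis section plans a repeated-measures ANOVA comparing change over time between groups. It names no term for branch. Under Trial design, only the outcome assessors are blinded.

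**The concern.** A single sequence used in order of inclusion is the usual description of simple randomisation, and a single list argues against separate lists for each branch. Such a list gives 65 per arm only on average. The sample size section nevertheless gives 65 as the size of each arm.

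Branch is the second issue. The treatments are delivered and individually tailored by physiotherapists, so branch could plausibly be related to outcome. If chance gives one device arm a larger share of patients from one branch, any branch difference enters the device comparison, and the analysis as described has no term to remove it. At stake are some precision and the credibility of the arm comparisons. The validity of the test is not in question.

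**Working it through.** **Inputs.** 195 patients, three arms, 65 per arm, 153 evaluable, effect size 10%, 80% power, alpha 0.05, five assessments (Sample size). Two branches (Study setting). Assumptions, because the article does not give them: independent 1:1:1 assignment, the split of patients between branches, and the correlation among repeated POMA scores.

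**The plan's own figure.** "the overall sample size needed to capture this effect size is of 153 subjects" is reproduced by reading the 10% as Cohen's f = 0.10 with correlation 0.5. The noncentrality is f² × N × m / (1 − ρ) = 0.01 × 153 × 5 / 0.5 = 15.3, with (3 − 1)(5 − 1) = 8 and (153 − 3)(5 − 1) = 600 degrees of freedom. Power is 0.803. The figure 195 / 3 = 65 then assumes equal arms. The total of 195 is taken as given here.

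**Arm sizes under simple randomisation.** The arm counts are multinomial (195; 1/3, 1/3, 1/3).

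- SD of one arm: √(195 × 1/3 × 2/3) = 6.6; central 95% range 52 to 78.
- Probability of exactly 65/65/65: 0.0042.
- Largest minus smallest arm (simulation): median 13, 95th percentile 27; at least 10 in 68% of realisations, at least 15 in 41%.
- Some arm with 55 or fewer: 22%. Some arm below 51 (= 153 / 3) before any dropout: 3.8%.

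**Effect on power.** Take a pairwise comparison with 80% power at 65:65. The standardised difference is (1.960 + 0.842) × √(2/65) = 0.491. Power at sizes a and b is Φ(0.491 / √(1/a + 1/b) − 1.960).

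| Arms | √(1/a + 1/b) | Power |
|---|---|---|
| 65:65 | 0.1754 | 80.0% |
| 55:75 | 0.1775 | 79.1% |
| 52:78 | 0.1790 | 78.4% |

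**Balance by branch.** The table gives the probability that the share of Fermo patients differs by more than 10 percentage points between the highest and lowest arm, for assumed Ancona:Fermo splits.

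| Split | Simple randomisation | List with exactly 65 places per arm |
|---|---|---|
| 50:50 | 0.50 | 0.49 |
| 70:30 | 0.44 | 0.43 |
| 80:20 | 0.34 | 0.33 |
| 90:10 | 0.14 | 0.13 |

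Fixing the totals barely changes this. In an assumed branch of 40 or 60 patients, the largest arm is at least 1.5 times the smallest in 57% and 44% of realisations under simple randomisation. With fixed totals of 65 the figures are about 50% and just over 30%.

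**What branch imbalance could add.** Assume a branch effect of 0.5 SD and a smaller branch of 40 to 60 patients. Chance imbalance then contributes an SD of about 0.035 to 0.041 to an arm difference whose standard error is √(2/65) = 0.175. As a share of variance this is (0.035 / 0.175)² ≈ 4% to (0.041 / 0.175)² ≈ 5%.

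**The case against.** The strongest reply is that simple randomisation is valid. Its error rates already allow for chance imbalance, and the power cost is one to two percentage points. That stands, and it sets the size of this point.

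A reader might infer that the design cannot deliver 65 per arm. The documents do not support this. Equal arms are improbable under simple randomisation but possible, and the text does not exclude a list built with 65 places per arm, which would give 65 exactly once all 195 are enrolled. The 0.4% chance of exact equality should not be pressed either: branch-stratified blocks of 3, 6 or 9 give exactly 65/65/65 in only 55%, 31% and 23% of simulations. Their merit is that they bound the gap.

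A reader might also infer that device is confounded with branch because different therapists work at each site. The article does not say that staff or case-mix differ; it describes one clinical unit with two branches.

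Finally, an article may leave blocks and strata to the full protocol, and covariates to the analysis plan. Neither is shown, so such details may exist. The Recruitment section does, however, state a method, and that method as described secures neither the arm sizes nor balance by branch.

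**Conclusion.** The point holds in a limited form. The allocation method as described does not ensure 65 per arm: if it is simple randomisation, a gap of 13 between largest and smallest arm is typical and 27 is the 95th percentile. It leaves balance between Ancona and Fermo to chance whether or not the totals are fixed, and the described ANOVA has no branch term. The effect is a small, avoidable loss of precision, with no systematic bias and no error in the total of 195.

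The arm-size figures assume independent 1:1:1 assignment, which is a fair reading but is not stated. The branch figures depend on an assumed split, and their importance depends on an assumed branch difference in outcome. The case for acting rests on how little the remedy costs.

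**What to change.** **Analysis, for all patients including those already randomised.** Specify branch as a covariate in the primary POMA model and adjust post-treatment POMA for baseline POMA. Model the end-of-treatment, 6-month, 1-year and 2-year values as the outcomes. Baseline should not be a covariate while it is also one of the repeated outcomes, so the five-assessment ANOVA has to be restructured. No new data are needed.

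**Allocation, for any patients still to be enrolled.** Use concealed, computer-generated permuted blocks of varying size, stratified by branch. Very short blocks should be avoided: only assessors are blinded, so recruiting staff could predict some assignments. Used for all 195 patients, blocks of 6 would hold the largest-minus-smallest gap to 3 and blocks of 9 to 6. Introduced part-way, they do not undo imbalance already present.

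**Wording.** State whether the existing list has blocks, strata or fixed totals. If it has none and is kept, describe 65 per arm as an expected number.

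**Cost.** A short amendment, two randomisation phases to report, and some remaining predictability within blocks. The article gives recruitment as ending in August 2021 and data collection as already under way, so the number of patients a new list could still reach is unknown. The analysis change does not depend on it.
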